#### Allocation

Participants will be randomly assigned to either a control or intervention group with a 1:1 allocation as per a computer-generated randomisation schedule stratified by site in the online REDCap database. Randomisation will be performed immediately following the collection of the necessary baseline data.

#### Blinding

Due to the nature of the intervention, neither participants nor staff will be blinded to allocation.

#### Data collection methods: primary outcome

Primary endpoint variables are collected from Swedish healthcare registers as specified in table 3.

**Table 3 T3:** Primary outcomes

Variable	Coding International Classification of Diseases 10th Revision	Source	Validity
Ischaemic stroke	I63	Riksstroke	High
Stroke not specified	I64	Riksstroke	High
All-cause mortality	N/A	National register of death	Very high
Intracerebral bleeding (spontaneous)	I61	Riksstroke	High

#### Data collection methods: secondary and exploratory outcomes

Variables collected for secondary and exploratory outcomes are reported in table 4.

**Table 4 T4:** Secondary outcomes

Variable	Coding International Classification of Diseases 10th Revision		Source
Myocardial infarction	I21, I22, I25.2		National inpatient register, Riksstroke
Major bleeding	Gastrointestinal bleeding	K226, K250, K252, K254, K256, K260, K262, K264, K266, K270, K272, K274, K276, K280, K282, K284, K286, K290, K625, K661, K920, K921, K922, I850 and I983	
	Urogenital bleeding	N02, R319, N939, N950 and N501A	
	Other bleeding	H113, H313, H356, H431, H450, H922, I312, J942, M250, R04, R58, T810, D500, D629 and T792	
	Subdural, epidural and subarachnoid haemorrhages (including traumatic)	I60, I61, I62, S064, S065 and S066	
	Procedure codes for transfusion	DR029, DR033 and Z513	
Atrial fibrillation/flutter	I48		
Pacemaker implantation	FPE00, FPE10, FPE20 and FPE26		
Oral anticoagulation and antiplatelet treatment, non-steroidal anti-inflammatory drug	B01A, N02BA and M01A		National drug dispense register

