**Trial registration number:**

NCT05134454.

STRENGTHS AND LIMITATIONS OF THIS STUDYFirst register-based randomised clinical trial on secondary preventive ECG screening poststroke/transient ischaemic attack with stroke and all-cause mortality endpoints.Participants were included from a national network of stroke units and central adjudication of ECG recordings in the intervention arm.Robust inclusion criteria mirror the clinical real-world population; age at least 70 years for inclusion.The Swedish stroke register (Riksstroke) is used for the provision of the majority of baseline data.Endpoints from healthcare registers will not be further adjudicated.

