### Key secondary objectives

The key secondary objectives are to estimate the treatment effect on the primary outcome and determine if there are any differences between extended and standard ECG screening for:

Ischaemic stroke.All-cause mortalityIntracranial bleedingMajor bleeding.Myocardial infarction.Pacemaker implantation.Cost-effectiveness.

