### Eligibility criteria

#### Inclusion criteria

Patients aged ≥70 years admitted to a stroke unit with a diagnosis of ischaemic stroke or TIA within 14 days of inclusion. Stroke is clinically defined as the acute onset of a focal neurological deficit of presumed vascular origin lasting for ≥24 hours or resulting in death. Stroke is further categorised as ischaemic or as intracerebral or subarachnoid haemorrhage based on CT and/or MRI of the brain. TIA is defined as a sudden, focal neurological deficit of presumed vascular origin with transient symptoms (<24 hours).^25^ Only patients with ischaemic stroke and TIA are eligible for inclusion.Signed informed consent.

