#### Exclusion criteria

Previously diagnosed AF.Contraindication to OAC treatment.Indication for anticoagulant treatment other than AF.Patients with a pacemaker, implantable cardioverter defibrillator or implantable loop recorder.Patients who, according to the investigator, will not be able to comply with the trial protocol.Previous participation in the AF SPICE trial.

The rationale for the age cut-off of 70 years in AF SPICE is partly due to the higher AF yield in elderly patients, as well as the increased benefit of OAC treatment in elderly patients in the case of AF detection. Notably, 74% of stroke patients in Sweden are aged 70 years or older, making the study population quite representative of future implementation. The recruitment window of 14 days is intended to give a margin for the occurrence of patient transfers between centres for thrombectomy, holidays and uncertainty about eligibility. Patients with a cardiac implantable device are excluded since their very long-lasting continuous heart rhythm monitoring will make them biased with a lower probability of AF detection on a surface ECG recording. Further, ventricular pacing will make reading the patch ECG difficult due to the lack of pacing annotations.

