#### Secondary endpoints

Individual components of the primary endpoint.Major bleeding, including intracranial bleeding.Myocardial infarction.Pacemaker implantation.Anticoagulation treatment.AF prevalence.Adherence to long-term ECG recording.Incidence of other prognostic arrhythmias during long-term ECG recording.

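### The myocardial infarction outcome includes I25.2, the code for old infarction, so infarctions from before randomisation can be counted as trial events

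*Protocol article*

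**What the plan says.** The protocol article lists "Myocardial infarction" among its secondary endpoints. It also appears under Key secondary objectives, among the outcomes for which the trial will "determine if there are any differences between extended and standard ECG screening for".

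The section on data collection for secondary and exploratory outcomes gives the operational definition: "Variables collected for secondary and exploratory outcomes are reported in table 4". That table is captioned as secondary outcomes, and its first row reads "Myocardial infarction I21, I22, I25.2", with the sources given as "National inpatient register, Riksstroke".

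Four other statements bear on how this row would work:

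- Strengths and limitations: "Endpoints from healthcare registers will not be further adjudicated".
- Exclusion criteria: these open with "Previously diagnosed AF.Contraindication to OAC treatment.Indication for anticoagulant treatment other than AF" and go on to cardiac devices, ability to comply and previous participation. Prior infarction is not among them.
- Inclusion criteria: "Patients aged ≥70 years admitted to a stroke unit with a diagnosis of ischaemic stroke or TIA within 14 days of inclusion".
- Baseline variables are described in separate sections that point to Riksstroke and the supplement, so Table 4 is not the baseline list.

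**The concern.** A key secondary objective that compares the arms needs events that happen after randomisation. I21 and I22 describe such events. I25.2 does not: in ICD-10, the classification that Table 4 names, it means an old myocardial infarction. It records that a patient once had an infarction, and it can be entered at an admission for something else.

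The trial enrols people aged 70 or over with ischaemic stroke or TIA and does not exclude prior infarction, so some participants can be expected to carry that history. With no adjudication, the register code decides whether an event is counted. Patients are also included during the index admission, so an I25.2 code set at that discharge could be scored almost at once.

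Two things are at stake. The reported infarction rate would mix new events with history, and any real difference between the arms would be diluted. The date attached to a history code also reflects when the patient was next admitted, not when an infarction occurred, which matters because the main analysis is time to event.

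**Working it through.** **Is the row an outcome definition?** Yes. The text introduces Table 4 as holding secondary and exploratory outcome variables, the caption says the same, and no other place in the article defines the infarction endpoint. Table 3 is a useful contrast: the primary outcome uses I63, I64, I61 and death, with no history code.

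**Does anything screen out old infarctions?** No section restricts I25.2 to baseline use, to patients without an earlier infarction, or to infarctions dated after randomisation. A rule counting only codes dated after randomisation would not be enough, because an old infarction coded at a later admission carries a later date.

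**Size.** The protocol states no infarction rate, effect or power, so there is no figure to reproduce. All of the following inputs are assumptions:

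- True incidence 1.5% per year, so 3-year risk q = 1 − exp(−0.045) = 0.0440.
- History of infarction h = 5%, 10% or 15%.
- Share of those with I25.2 recorded in follow-up r = 25%, 50% or 75%.
- True risk ratio RR = 0.80.
- h and r equal in both arms.

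Formulas, for the control arm unless stated:

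- False events = h·r·(1 − q)
- Counted risk = q + h·r·(1 − q)
- False share = false events / counted risk
- Counted risk, intervention arm = RR·q + h·r·(1 − RR·q), with RR·q = 0.0352

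| h, r | h·r | False events | Counted risk, control | False share | Counted risk, intervention | Apparent RR |
|---|---|---|---|---|---|---|
| 5%, 25% | 0.0125 | 0.0120 | 0.0560 | 21% | 0.0473 | 0.84 |
| 10%, 50% | 0.0500 | 0.0478 | 0.0918 | 52% | 0.0834 | 0.91 |
| 15%, 75% | 0.1125 | 0.1076 | 0.1516 | 71% | 0.1437 | 0.95 |

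The counted 3-year risk is thus 5.6–15.2% where the true risk is 4.4%.

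**Effect on power.** This is a second illustration, using the protocol's 1631 per arm and two-sided 5%. Let m be the share of patients counted only because of an old infarction, so that counted risk = m + (1 − m)·q, with true RR 0.80.

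| Control q | m | Apparent RR | Power | False share, control arm |
|---|---|---|---|---|
| 4% | 0 | 0.80 | 23% | 0% |
| 4% | 2% | 0.87 | 16% | 34% |
| 4% | 15% | 0.96 | 7% | 82% |
| 6% | 0 | 0.80 | 33% | 0% |
| 6% | 2% | 0.85 | 25% | 25% |
| 6% | 15% | 0.95 | 11% | 75% |

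The two sets of assumptions agree on the direction and give a similar range for the apparent ratio.

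**The case against.** **Table 4 may be partly a register extraction list.** It also holds antiplatelet and anti-inflammatory drug codes, which are not named endpoints, and it does not say how events are dated or how history is handled. Those rules often sit in an analysis plan, which is not shown. This stands as a caution: the article permits history to be counted but does not spell out a rule that does so. It does not remove the problem, because the code list is stated, not omitted, and it is the only definition of this endpoint in the article.

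**The size is assumed throughout.** This stands. The protocol does not say how often I25.2 is recorded in the Swedish registers, and a true ratio of 0.80 has no support in it. Taking 0.91 instead, by analogy with the 9% reduction stated for the composite endpoint, the same formulas give an apparent ratio of 0.93–0.98. If there is no true effect, equal false events leave the ratio at 1.

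**The consequence is limited.** This also stands. The trial is not sized for infarction, and on the assumptions above power is only 23–33% even with the code removed.

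**Deletion could lose real events.** I25.2 can follow an infarction that occurred during the trial. However, an in-trial infarction treated in hospital should already appear as I21 or I22. I25.2 alone cannot show whether an infarction came before or after randomisation, nor when it occurred.

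**Conclusion.** The concern holds. As written, the infarction outcome contains a history code, and nothing else in the article stops infarctions from before randomisation being scored as events. The direction, an inflated rate and a ratio pulled towards 1, follows if history is recorded equally often in both arms. Randomisation balances the history itself. Equal recording is an added assumption, because it depends on later admissions in an unblinded trial.

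The size is illustrative and cannot be pinned down from the protocol. It ranges from modest to severe depending on how common prior infarction is and how often it is coded. The defect is confined to this one secondary endpoint; the primary endpoint and the sample size are untouched. It should be corrected before outcome data are extracted.

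**What to change.** In Table 4, remove I25.2 from the myocardial infarction outcome. Define the outcome as an admission coded I21 or I22 with an admission date after randomisation. Keep I25.2 as a baseline comorbidity variable only.

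The cost is one code in the definition, with no new data and no change to patient procedures. The reported infarction rate will be lower, and a few in-trial infarctions recorded only under I25.2 may be missed.

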#### Baseline data entered at the inclusion of all participants

Data entered at baseline for all participants are listed in the online supplemental table. The remaining baseline variables will be collected from the Riksstroke register.^5^

#### Baseline data entered in the control and intervention arms

Data entered at baseline in the standard and intervention arms are listed in the online supplemental appendix.

#### Baseline register data from the Riksstroke register

Baseline data from Riksstroke are listed in the online supplemental appendix.

#### ECG data

There are different ECG variables for the control and intervention arms (online supplemental appendix).

In the control arm, the local investigator or delegate will report if ECG was recorded using ECG telemetry and/or Holter recording, the duration of each recording and whether AF was diagnosed.In the intervention arm, ECG data from patch recordings will be stored in the patch hardware and returned by the participant by mail. Data from ECG patch hardware will be uploaded by the patch provider into the Cardiologs database. ECG patch data will be scrutinised by the core reading team, which also enters ECG data manually into the REDCap database.

For the second ECG patch recording initiated 2–4 months following randomisation, data will be collected on whether the patch is applied within healthcare or by the participant.

#### Cost-effectiveness

The cost-effectiveness analysis will be based on a Markov cohort model where the prevalence of AF, use of OACs, clinical events and all-cause mortality will be collected from the AF SPICE study. The cost of clinical events, age-specific utilities and stroke deaths will be collected from the literature. The number of gained life years, quality-adjusted life years and cost of the screening process will be calculated.

#### Retention

At the majority of included sites, the second visit for the intervention group coincides with an outpatient follow-up visit after the stroke, which will give the participant motivation to attend the visit. Patients receive no reimbursement for participation.

### Statistical methods

The main analysis of the outcome will be based on time to event (endpoint) and performed according to the intention to treat principle. The cumulative incidence of the combined endpoint and its individual components will be presented for each treatment group (standard and extended ECG).

For the primary analysis of the combined endpoint, the log-rank test will be used to test for treatment group differences. Cox proportional hazard regression will be used to estimate the hazard ratios with 95% CIs and to analyse associations with AF incidence and/or effect modification by age, comorbidity, biometrics and supraventricular activity.

The secondary analysis of each individual component of the primary endpoint will account for competing risks. We will use cause-specific models (where the rate of each individual endpoint is based on patients who have not yet experienced any of the endpoints) and subdistributional hazard models (where the rate is based on patients who have not yet experienced the endpoint under study). Other analysis, including baseline characteristics, will be presented by proportions (binary variables) and means (continuous variables) with 95% CIs in each ECG group. Corresponding group comparisons will be carried out by χ^2^ tests and t-tests. An outcome with a p value <0.05 will be considered statistically significant.

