#### Sample size

The sample size was calculated based on the primary outcome.

There were very few studies available with outcome data matching the age and morbidity of the AF SPICE trial. Very few studies on patients with an index stroke incident were available; in particular, there was a lack of data regarding patients with recent strokes and AF without OAC treatment. For this, we have made estimations and extrapolations using the very few available studies on patients with AF without OAC treatment. In particular, extrapolations have been made with regard to age since most available studies have included patients considerably younger than what is expected in AF SPICE. A list of studies used in sample size estimations is available in online supplemental appendix.

10.1136/bmjopen-2023-073470.supp1Supplementary data

For the estimations of AF detection proportions, available studies on short-term (48±24 hours) ECG recordings following stroke and corresponding studies on long-term (14 days) recordings were used. As with the outcome data, no studies with similar populations and ECG recording durations were available. Furthermore, the AF detection/incidence was estimated for the entire follow-up for both arms, reflecting the additional detection within standard care after the index event, thereby reflecting the actual risk exposure in both arms during follow-up. A list of the AF detection studies available for this estimation is reported in online supplemental appendix.

The assumptions for the sample size calculation are reported in table 2. The complete sample size calculation is provided in the appendix. For the yearly risk of the composite endpoint, we estimate 17% in patients with AF and no OAC treatment, 7.3% in patients with AF and OAC treatment and 5% risk in patients without AF. We further estimate an AF detection proportion of 6% in the control group and 19% after two ECG recordings in the intervention group, and 13% with untreated AF in the control group, resulting in a sample size of 2718 for 3 years of fixed follow-up time after inclusion. Adding 20% for participant dropouts and treatment discontinuation, a total sample size of 3262 is needed, corresponding to 1631 in each arm based on 3 years of follow-up, 80% power and a double-sided significance level of 5%. The study is powered to detect a 9% reduction in the composite endpoint in the group with extended ECG screening.

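### Randomisation is stratified by site, but the stated primary log-rank test and Cox hazard ratio name neither site nor age adjustment; the test is valid and a small efficiency gain is available

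*Protocol article*

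**What the plan says.** Under Allocation, patients are assigned with "1:1 allocation as per a computer-generated randomisation schedule stratified by site in the online REDCap database". Site is the only stratification factor named; age is not one.

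Under Statistical methods, the primary test is fixed as follows: "For the primary analysis of the combined endpoint, the log-rank test will be used to test for treatment group differences". The effect estimate comes from a second method: "Cox proportional hazard regression will be used to estimate the hazard ratios with 95% CIs". The same sentence gives the Cox model a further use, to study "effect modification by age, comorbidity, biometrics and supraventricular activity". Neither sentence mentions a site stratum or an adjustment covariate for the main treatment comparison.

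**The concern.** The usual practice is to carry a randomisation stratum into the primary analysis, and to adjust for a strong baseline predictor of the outcome. Here the composite includes death from any cause in patients aged 70 or older with no stated upper age limit. The Sample size section itself extrapolates event risks for age. Age and index event (stroke or TIA) are both known at randomisation because they determine eligibility.

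Naming age as an effect modifier does not do this job. An interaction asks whether the effect differs by age; adjustment uses age to sharpen the main comparison.

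What is at stake is efficiency. If sites differ in baseline risk, an unstratified test leaves some power unused. If age is strongly prognostic, an unadjusted proportional hazards analysis also has somewhat less power than an adjusted one. All the data needed are already collected.

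**Working it through.** **1. Effect size implied by the plan.** The Sample size section gives these yearly risks: "we estimate 17% in patients with AF and no OAC treatment, 7.3% in patients with AF and OAC treatment and 5% risk" without AF. It gives these proportions: "AF detection proportion of 6% in the control group and 19% after two ECG recordings in the intervention group, and 13% with untreated AF" in controls.

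- Control: 0.06 × 7.3% + 0.13 × 17% + 0.81 × 5% = 0.438 + 2.210 + 4.050 = 6.698% per year.
- Intervention: 0.19 × 7.3% + 0.81 × 5% = 1.387 + 4.050 = 5.437% per year.
- Ratio: 5.437 / 6.698 = 0.812.

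**2. The plan's own sample size.** The inflation step reproduces: 2718 × 1.2 = 3261.6, hence 3262. The 2718 does not. With three-year risks taken as three times the yearly risks (20.09% v 16.31%), the hazard ratio is ln(1 − 0.1631) / ln(1 − 0.2009) = 0.794. Schoenfeld's formula then gives 4 × (1.960 + 0.842)² / (ln 0.794)² ≈ 589 events, and 589 / 0.182 ≈ 3236 patients. Other two-sided forms at 80% power also gave more than 2718. That discrepancy does not depend on stratification and is a separate matter. Only the ratio of 0.812 is used below.

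**3. Simulation.** From the documents: 3262 patients, 30 sites, 1:1 randomisation within site, three years of follow-up, hazard ratio 1.0 or 0.812. Assumed, because the documents give no figure: between-site SD of the log hazard 0 to 0.5, age hazard ratio 1.0 to 2.5 per 10 years, age mean 79 and SD 6, permuted blocks of 4, unequal site sizes. There were 1000 trials per setting in the first and third rows and 1500 in the others. All four tests were applied to the same simulated trials.

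Power at hazard ratio 0.812:

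| Site SD | Age HR per 10 years | Plain log-rank | Log-rank by site | Cox + age | Cox + age, by site | Gain, site | Gain, site + age |
|---|---|---|---|---|---|---|---|
| 0 | 1.0 | 70.1% | 69.8% | 70.0% | 69.9% | −0.3 | −0.2 |
| 0.2 | 1.5 | 67.5% | 68.1% | 68.3% | 68.3% | +0.6 | +0.8 |
| 0.2 | 1.8 | 68.4% | 68.6% | 69.1% | 68.9% | +0.2 | +0.5 |
| 0.3 | 2.0 | 68.5% | 68.8% | 68.9% | 69.7% | +0.3 | +1.2 |
| 0.3 | 2.5 | 66.0% | 66.3% | 68.2% | 69.1% | +0.3 | +3.1 |
| 0.5 | 2.0 | 63.7% | 65.7% | 65.8% | 67.8% | +2.0 | +4.1 |

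Gains are in percentage points over the plain log-rank test. In the row with age HR 2.5, age alone gives 68.2 − 66.0 = 2.2 points and site alone 0.3. Only at site SD 0.5 do site (2.0) and age (65.8 − 63.7 = 2.1) contribute about equally. As a squared ratio of mean test statistics, the largest gains equal about 4% of sample size for site alone (1.042) and 8% for site plus age (1.077).

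The fall in plain log-rank power down the table is consistent with 0.812 acting within site and age. The rows compare analyses and are not forecasts of this trial's power.

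**4. Validity.** At hazard ratio 1.0, the plain log-rank test rejected in 5.4%, 4.6%, 5.0%, 4.4%, 4.9% and 4.3% of trials, in the order of the table. With 1500 trials the Monte Carlo standard error at 5% is √(0.05 × 0.95 / 1500) = 0.56 points, so 4.3% is about 1.2 standard errors below nominal. The Cox model with age, stratified by site, rejected in 4.7% to 5.7%.

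**The case against.** The strongest objection is that silence is not a decision. A log-rank test can be stratified, the text never says unstratified or unadjusted, and a condensed article often leaves strata and covariates to an analysis plan, which is not shown here. This stands in part: a reader might infer that the trial has chosen to ignore site and age, and the documents do not support that. But the protocol does not leave the primary test open. It names it, and an unqualified log-rank test is ordinarily the unstratified one.

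A second objection is that the gain is small and assumed. This stands. With no heterogeneity there is none, and stratifying the log-rank test by site alone would rarely be noticed. The larger gains need strong site or age effects that the documents do not report.

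A third is that an unadjusted hazard ratio closer to 1 is not biased. It is marginal, the adjusted one is conditional, and a marginal comparison does answer a question about the difference between arms. This also stands, so attenuation is not used here as a fault.

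Two further stronger readings are tempting. One is that an unstratified test after stratified randomisation is invalid; the null rejection rates do not support that. The other is that this change would make good the shortfall against the claimed 80% power; a gain of at most about 4 points would not.

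**Conclusion.** The stated primary analysis is valid but does not name the design's own stratum or use a baseline predictor already held. This is a minor efficiency and clarity point. Within the assumed range (site SD 0 to 0.5, age hazard ratio 1 to 2.5 per 10 years), site is worth about 0 to 2 points of power and site plus age about 0 to 4, mostly from age. The textual observation is certain; the size of the gain is not, since it depends wholly on prognostic strengths that the documents do not give. Adjustment for index event was not simulated, so no gain is claimed for it.

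**What to change.** Before outcome data are examined, state that the primary p-value and the primary hazard ratio come from the same Cox model, stratified by site and adjusted for age and index event (stroke v TIA). Using one model avoids a p-value and a confidence interval that disagree, and it secures the age contribution, which a log-rank test stratified only by site would not. Fix the rule for pooling small sites in advance. Keep the plain log-rank test and the unadjusted hazard ratio as sensitivity analyses.

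The cost is wording, with two downsides to acknowledge. The primary hazard ratio becomes conditional on site, age and index event, and should be reported as such. Sites with very few events also contribute little: an average site has 3262 / 30 ≈ 109 patients, and at three-year risks of 18.2% and 15.05% (the yearly rates of step 1 taken as exponential hazards) about 109 × 16.6% ≈ 18 events, but small sites will have far fewer. If an existing analysis plan already specifies this, add one clause to the public text and change nothing else.

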## Introduction

Ischaemic stroke is one of the leading causes of mortality worldwide and a major cause of permanent disability in adults.^1^ Despite the implementation of novel treatment strategies, morbidity and mortality remain significant.

Modifiable risk factors for stroke include hypertension, atrial fibrillation (AF), hyperlipidaemia, smoking and diabetes.^2 3^ Several of these risk factors have been undetected for a long time since they remain asymptomatic.

During 2018, the stroke incidence in Sweden was 223 per 100 000 in men and 191 per 100 000 in women.^4^ At the 3-month follow-up poststroke, 26% were deceased or dependent on activities of daily living.^4 5^ The risk for stroke recurrence is highest during the first 3–6 months following admission, and the 1-year recurrence risk has been reported to be 3–5%.^6 7^

The societal burden of the disease is significant. Disability with a need for long-term care, and in younger patients, impaired work ability entails enormous societal costs.^8^ Strokes due to AF are more severe and have significantly higher mortality than other stroke cases.^9^

AF is the most prevalent clinical arrhythmia, with a steeply increasing incidence with advancing age.^10^ AF is also one of the strongest risk factors for stroke.^3^ However, the increased stroke risk associated with AF can be markedly reduced by oral anticoagulation (OAC) treatment.^11^ Unfortunately, AF is paroxysmal and asymptomatic in a significant proportion of stroke patients, leading to lower detection rates and frequently leaving stroke survivors with an undiagnosed and untreated risk factor and a higher risk of stroke recurrence.^12^ Despite this, no study so far has reported evidence of the benefit of ECG AF screening in terms of reduced stroke recurrence and mortality after a stroke event.

Randomised controlled trials^13^ (CRYSTAL-AF^14^ and EMBRACE^12^) have shown that prolonged ECG monitoring compared with standard of care (at the time of 24-hour ECG) increased detection of AF in patients with cryptogenic stroke.

The FIND-AF_randomised_ trial^15^ also showed increased detection of AF and included a broader group of participants, suggesting that prolonged ECG monitoring should be used in all patients with ischaemic stroke.

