## Methods and analysis

### Primary objectives

To determine if extended continuous ECG screening (14+14 days) is superior to standard ECG screening (48±24 hours, that is, range 24–72 hours) in reducing the risk of the combined endpoint of ischaemic stroke, intracerebral bleeding and all-cause mortality in elderly patients admitted to the hospital for ischaemic stroke or TIA.

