### Outcomes

#### Primary endpoint

Difference between the two arms in a combined endpoint of recurrent ischaemic stroke, intracerebral bleeding and all-cause mortality during at least 36 months of follow-up.

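### The stated cause-specific risk set turns the all-cause mortality component into death as first event, and drops bleeds after strokes and strokes after bleeds

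*Protocol article*

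**What the plan says.** The primary endpoint is a "combined endpoint of recurrent ischaemic stroke, intracerebral bleeding and all-cause mortality during at least 36 months of follow-up". The Secondary endpoints section then lists "Individual components of the primary endpoint". All-cause mortality also appears by name among the Key secondary objectives. Neither list limits it to deaths without an earlier stroke or bleed. The primary outcomes table takes deaths from the "National register of death", so deaths at any point in follow-up are available.

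The analysis of the components is fixed under Statistical methods: "The secondary analysis of each individual component of the primary endpoint will account for competing risks". Two models are named. The first is "cause-specific models (where the rate of each individual endpoint is based on patients who have not yet experienced any of the endpoints". The second is "subdistributional hazard models (where the rate is based on patients who have not yet experienced the endpoint under study". The article describes no group comparison based on all deaths regardless of earlier events.

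**The concern.** A competing event is one that prevents the event of interest. Death prevents a later stroke, but a non-fatal stroke or intracerebral bleed does not prevent death, and neither of them prevents the other. The stated rule nevertheless lets every component end follow-up for every other component.

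The deaths lost are not a random subset. The Introduction says: "Strokes due to AF are more severe and have significantly higher mortality than other stroke cases". Detecting AF and anticoagulating is expected to save lives largely by preventing such strokes, and intracerebral bleeding is a main hazard of anticoagulation. Deaths that follow a recorded stroke or bleed lie on exactly these two pathways. A mortality hazard ratio that leaves them out answers a different question from the one in the objectives and could mislead on net benefit.

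**Working it through.** The document attaches no figure to this point, so there is none to reproduce. The core of the check is a reading of the risk sets; the arithmetic only illustrates size.

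**Risk sets.** Take a patient with a non-fatal ischaemic stroke at month 6 who dies at month 20.

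- Cause-specific model as stated: the patient leaves the risk set at month 6, and the death is not an event.
- Subdistribution model, standard form: the stroke is the competing event. The patient stays in the risk set, but the death is still not an event.
- Subdistribution model, literal reading of the parenthesis: the patient has not yet had the endpoint under study, so the death might count. The two models would then count different deaths under one label.
- Unrestricted all-cause mortality, as listed in the objectives: the death counts.

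Replace the death with an intracerebral bleed at month 20, and the first two lines apply to the bleeding component in the same way.

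**Share of deaths lost, control arm, 3 years.** Inputs from the protocol:

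- Yearly composite risks of 7.3% (AF with OAC), 17% (AF without OAC) and 5% (no AF), from Sample size.
- Control-arm proportions of 6% detected and 13% untreated AF, from Sample size, leaving 100 − 6 − 13 = 81% without AF.
- 1631 patients per arm, from Sample size.
- One-year stroke recurrence of 3–5%, from the Introduction.

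Assumptions not in the documents: constant hazards; the 3–5% used as the yearly hazard s of a first stroke or bleed; death hazard afterwards m times the event-free death hazard d, with m from 1 to 5.

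Composite risk: 0.06 × 7.3% + 0.13 × 17% + 0.81 × 5% = 6.70% per year. Hazard λ = −ln(1 − 0.0670) = 0.0693, and d = λ − s.

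- Deaths as first event: D1 = (d/λ)(1 − e^(−3λ))
- Deaths after a stroke or bleed: D2 = (s/λ)(1 − e^(−3λ)) − s[e^(−3λ) − e^(−3md)]/(md − λ)
- Share lost: D2/(D1 + D2)

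Example with s = 0.05, d = 0.0193, m = 5: 1 − e^(−3λ) = 0.1878, D1 = 0.0524, D2 = 0.0185, share = 0.0185/0.0709 = 26.1%.

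| s per year | d per year | m = 1 | m = 2 | m = 3 | m = 5 |
|---|---|---|---|---|---|
| 0.03 | 0.0393 | 4.3% | 7.9% | 11.1% | 16.1% |
| 0.04 | 0.0293 | 5.7% | 10.5% | 14.6% | 21.2% |
| 0.05 | 0.0193 | 7.1% | 13.0% | 18.0% | 26.1% |

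Multiplied by 1631, this is about 6 to 35 uncounted deaths out of totals between about 92 and 207.

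**Effect on the comparison (hypothetical).** Suppose screening lowers s from 0.05 to 0.035 and leaves d at 0.03, with m = 3 to 5.

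- All deaths per person-year: 0.0340 against 0.0328 at m = 3, ratio 0.97; 0.0376 against 0.0354 at m = 5, ratio 0.94.
- First-event cause-specific rate: 0.03 in both arms, ratio 1.00.
- Three-year cumulative incidence of death as first event: (0.03/0.08)(1 − e^(−0.24)) = 0.0800 against (0.03/0.065)(1 − e^(−0.195)) = 0.0818, ratio 1.02.

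A mortality benefit that works through stroke prevention is invisible on the cause-specific scale and slightly reversed on the cumulative-incidence scale.

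**The case against.** A first-event cause-specific breakdown is a legitimate decomposition: the component hazards add up to the composite hazard, and the article discloses the risk set openly. That stands, and it is a reason to keep the breakdown under a correct label. It does not make the breakdown an analysis of all-cause mortality.

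The second model's wording keeps patients with an earlier stroke or bleed at risk of death. That is also true, but being at risk is not the same as having the death counted. The standard model does not count it, and the literal alternative leaves two inconsistent mortality results.

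Mortality also enters through the promised cumulative incidence of the components, the cost-effectiveness model and a win ratio analysis. None of these is stated to exclude later deaths, so the restriction is shown for the component models and not for every mortality result. Equally, none is described as an all-deaths comparison; the win ratio's hierarchy is not given.

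The article is condensed and the SAP is not shown, so a reader should not infer that no all-deaths analysis is planned anywhere. The point here is not an omission: the article states a rule, and that rule does not fit the endpoint to which it is applied.

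**Conclusion.** The point holds for the secondary analysis of the components. Followed as written, the cause-specific model estimates death as first event, and the accompanying subdistribution model does not repair this. The stroke and intracerebral bleeding components lose events that follow the other type.

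This conclusion is definitional and needs no assumed rate. The size does: about 4–26% of three-year control-arm deaths, given constant hazards, 3–5% per year for stroke or bleed and a post-event mortality ratio of 1–5. The Introduction says that recurrence risk is highest in the first 3–6 months, so carrying the one-year figure over three years is a simplification.

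Three stronger readings are tempting and not supported:

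- That the primary result is compromised. It is not: time to first composite event is the same under either component rule, and the strokes and bleeds preceding the uncounted deaths already count there.
- That close to half of deaths would be lost. With 5% stroke, 2% stroke-free death and 30% post-stroke death per year the share reaches 47%, but that is a 15-fold mortality ratio and the documents give no post-stroke death rate to support it.
- That major bleeding, myocardial infarction and pacemaker implantation are mis-specified too. The quoted rule covers only the components of the primary endpoint.

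**What to change.** Amend the component paragraph under Statistical methods, and the SAP to match, before outcome data are analysed:

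1. All-cause mortality: count every death from randomisation to the end of follow-up, with Kaplan-Meier curves, a log-rank test and an ordinary Cox model, and no censoring at stroke or bleed. Nothing competes with death from any cause, so no subdistribution model is needed.
2. Ischaemic stroke and intracerebral bleeding: for each, analyse the first event of that type whatever came before it, with death as the only competing event.
3. Keep the first-event breakdown if wanted, labelled as a descriptive decomposition of the composite, with its death line called death without prior stroke or intracerebral bleed.

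The cost is a few sentences. The events come from Riksstroke and the death register, which the trial already uses, so no extra data collection is needed and the primary analysis and sample size stay as they are.
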